# HALT (Hernia Active Living Trial): protocol for a feasibility study of a randomised controlled trial of a physical activity intervention to improve quality of life in people with bowel stoma with a bulge/parastomal hernia

**DOI:** 10.1186/s40814-020-00674-2

**Published:** 2020-09-24

**Keywords:** Parastomal hernia, Colostomy, Ileostomy, Bowel disease, Feasibility study

## Abstract

**Background:**

Parastomal hernia (PSH) can be repaired surgically, but results to date have been disappointing, with reported recurrence rates of 30 to 76%. Other types of intervention are therefore needed to improve the quality of life of people with PSH. One potential intervention is physical activity. We hypothesise that the intervention will increase core activation and control across the abdominal wall at a site of potential weakness and thus reduce the risk of PSH progression. Increases in physical activity will improve body image and quality of life (QoL).

**Methods:**

Subjects and sample

There were approximately 20 adults with a bowel stoma and PSH. People with previous PSH repair will be excluded as well as people who already do core training.

Study design

This is a feasibility study of a randomised controlled trial with 2 months follow-up, in 2 sites using mixed methods. Stage 1 involves intervention development and in stage 2, intervention and trial parameters will be assessed.

Intervention

A theoretically informed physical activity intervention was done, targeting people with PSH.

Main outcome of feasibility study

The main outcome is the decision by an independent Study Steering Committee whether to proceed to a full randomised controlled trial of the intervention.

Other outcomes

We will evaluate 4 intervention parameters—fidelity, adherence, acceptability and safety and 3 trial parameters (eligible patients’ consent rate, acceptability of study design and data availability rates for following endpoints):
I.Diagnosis and classification of PSHII.Muscle activationIII.Body composition (BMI, waist circumference)IV.Patient reported outcomes: QoL, body image and physical functioningV.Physical activity;VI.Psychological determinants of physical activity

Other data

Included are other data such as interviews with all participants about the intervention and trial procedures.

Data analysis and statistical power

As this is a feasibility study, the quantitative data will be analysed using descriptive statistics. Audio-recorded qualitative data from interviews will be transcribed verbatim and analysed thematically.

**Discussion:**

The feasibility and acceptability of key intervention and trial parameters will be used to decide whether to proceed to a full trial of the intervention, which aims to improve body image, quality of life and PSH progression.

**Trial registration:**

ISRCTN15207595

## Background

### Parastomal hernia

Parastomal hernia (PSH) is a common problem following stoma formation [1, 2], with prevalence estimates over 30% by 12 months, 40% by 2 years and 50% or higher at longer duration of follow-up [3]. A cross-sectional study of 75 patients with an end colostomy for ≥ 1 year found that 33 (44%) had evidence of a PSH on computerised tomography (CT) [4]. The majority of these patients were symptomatic (27 versus 6), such as pain or difficulties with stoma appliance and able to identify the moment of clinical appearance of the PSH, which occurred within 8 months of surgery [4].

One of the functions of deep abdominal muscles is to provide support to the abdominal region and the spine by forming a muscle band that tightens like a corset [5]. Following abdominal surgery, the physiology of the abdominal wall is altered with damage to nerve supply and atrophy of the midline muscular wall [6]. Surgery for creating a stoma alters the physiology in the same way and creates a further site of weakness by leaving a hole in the abdominal wall. Evidence indicates that there is muscular atrophy directly below the stoma site, resulting in change of forces and pressure on the abdominal wall [7].

There is a paucity of prospective data about the natural history and trajectory of PSH and whether PSH severity progression can be arrested [8, 9]. PSH can be repaired surgically but results to date have been disappointing, with reported recurrence rates of 30 to 76% [10]. The effectiveness of prophylactic synthetic mesh at the time of stoma formation for the prevention of PSH also remains uncertain [10]. Hence, other types of intervention are needed to improve the QoL of people with PSH. One potential intervention is physical activity.

People with a stoma have identified PSH and physical activity as top research priorities in relation to their quality of life (QoL) [11]. Studies highlight a trend toward inactivity after stoma formation surgery, with fear of PSH being a major deterrent to being physically active [12–14]. Both patient and surgical factors influence the risk of developing PSH [15]. Patient risk factors include high body mass index (BMI) [8, 16, 17], waist circumference [18] and low levels of physical activity [19, 20]. PSH is associated with poor body image (a psychological construct that captures the perceptions, emotions, and attitudes a person holds towards his/her own body [21]), and both PSH and poor body image are associated with poor general QoL [20, 22–26] and poor physical functioning [24, 25].

### Physical activity and parastomal hernia

To our knowledge, no physical activity intervention studies have been conducted that specifically target people with PSH. We hypothesise (see Fig. 1; logic model) that a physical activity intervention, that includes deep core muscle training, will elicit an adaptation response to re-engage muscle activation and control to provide an improved deep ‘corset’ support of the abdominal wall, thereby reducing the risk of PSH progression. Evidence shows that core activation leads to thickening on the abdominal muscles and a decrease in the cross-sectional area of the trunk (*p* < 0.001) [5] and that core training can lead to muscle thickening [27]. We also believe that a physical activity intervention will reduce the risk of PSH progression by effecting known risk factors for PSH such as BMI and low levels of physical activity.

**Fig. 1 Fig1:**
[figure not shown]
Logic model

There is no published research about the effect of physical activity in people with a stoma; hence, this hypothesis is based on evidence cited above as well as from systematic reviews and meta-analysis of the benefits of physical activity in the general population [28, 29]. For example, a systematic review of 10 studies (6 randomised controlled trials and 4 uncontrolled trials), involving people aged 60 to 80 years, of the effects of Pilates exercise training reported a large effect size (ES) to improve muscle strength (ES = 1.23), walking and gait performances (ES = 1.39), activities of daily living, mood states and QoL (ES = 0.94), moderate to high effect on dynamic balance (ES = 0.77), and small effects on static balance (ES = 0.34) and flexibility (ES = 0.31) [30]. A meta-analysis of 57 exercise interventions (mean age 30.4 years; standard deviation 15.35, range 10.02 to 63.40) reported that exercise resulted in improved body image from pre- to post-intervention for the intervention group compared with a control group with the largest effects evidence for adults (mean ES = 0.44) and older adults (mean ES = 033) [31].

However, before embarking on a full trial to test the hypothesis, a feasibility study of the proposed physical activity intervention and trial procedures is needed.

### Feasibility studies

The Medical Research Council framework for the development of complex interventions highlights that a key element of the development and evaluation process is feasibility work prior to assessing effectiveness [32]. It is generally recommended that feasibility studies descriptively evaluate a trial’s feasibility, acceptability and safety rather than test the effectiveness of the hypotheses of the planned main large-scale trial [33]. Feasibility studies are therefore conducted to assess key intervention and trial parameters to improve the rigor of a future full trial. In feasibility studies for instance, intervention fidelity and intervention adherence may be assessed because they can impact on statistical power and interpretation of trial results, including underestimating any efficacy in a full trial. However, a challenge for assessing these key parameters is that there is no consensus on the acceptable minimum fidelity or adherence level in trials and no standardised approach to their definition and measurement in the field of complex interventions [34, 35]. A recent review of how to define and measure adherence in studies examining older adults’ participation in exercise classes for instance, suggests adherence is defined and measured in a variety of ways with different cut-off points for indicating if adherence is successful [36].

### Aims

The aim of this feasibility study is to evaluate 4 intervention parameters—fidelity, adherence, acceptability and safety and 3 trial parameters, namely eligible patients’ consent rate, acceptability of study design (i.e., randomised controlled trial), and data availability rates for measuring the following endpoints (i.e., mechanisms and outcomes (see Fig. 1)) pre- and post-intervention:
I.Diagnosis and classification of PSHII.Muscle activationIII.Body composition (BMI, waist circumference)IV.Patient reported outcomes: QoL, body image and physical functioningV.Physical activityVI.Psychological determinants of physical activity

The aim of the future trial is to determine whether a structured physical activity intervention that includes core training and signposting to written guidance about physical activity in people who have bowel stoma and have PSH improves outcomes in comparison with signposting to written guidance only.

## Methods

### Project design

This is a feasibility study of a randomised controlled trial with 2 months follow-up, in 2 sites, with 20 participants, using mixed methods. Stage 1 involves intervention development and in stage 2, intervention and trial parameters will be assessed.

### Stage 1: intervention development

The research team have already developed a physical activity intervention for people with stoma [37] and produced an intervention manual for physical activity instructors supporting people with stoma to engage in physical activity [38]. In this study, the research team will develop new materials for people who have PSH, including videos to demonstrate exercises for re-engaging the body core and abdominal muscles and instructions on techniques and breathing for these exercises. A peer review group comprising exercise experts, physiotherapists and stoma nurse specialists will advise the research team during the development of these materials. The planned intervention is described below using the Template for Intervention Description and Replication (TIDieR) sub-headings and guidance, which is a generic template for behaviour change interventions [39]:

#### Why—theory and components

We hypothesise that a physical activity intervention that includes core training will elicit an adaptation response in the core muscles to re-engage muscle activation and control to provide an improved deep ‘corset’ support of the abdominal wall thereby reducing the risk of PSH progression. We also believe that a physical activity intervention will reduce the risk of PSH progression by effecting known risk factors for PSH, such as BMI and low levels of physical activity. The intervention is based on Self-Determination Theory [40] which focuses on maintaining the motivation to be physically active by making sure that participants have ‘autonomy’ (e.g., by offering a choice of different types of core body exercises), are ‘competent’ (e.g., by being shown how to lower intra-abdominal pressure during exercise) and experience ‘relatedness’ (e.g., by recognising their fears of worsening their bulge/PSH through exercise) [41].

#### What—materials

The exercise instructor will use the manual (i). Participants will be given materials that include videos demonstrating exercises for activating the body core and abdominal muscles and instructions on techniques and breathing for these exercises (ii). Participants will be given a biofeedback stabiliser to monitor and hence, regulate intra-abdominal pressure and risk of injury (iii).

#### What—procedures

The intervention will involve participants having 12 (1 per week) consultations with an exercise instructor. Professional associations for exercise specialists, such as the UK Chartered Institute for the Management of Sport and Physical Activity acknowledge that pre-exercise screening is an important part of the duties of an exercise specialist. Hence, the instructor will use the Physical Activity Readiness Questionnaire (PARQ) long version [42] so that she can prescribe an individualised exercise programme for each participant, taking account of medical history and current health status. Participants will be prescribed 4 different types of core training exercises with 4 levels of progression. These exercises are based on the Australian Physiotherapy and Pilates Institute methods programme [43]. Over the 12-week programme, there will be gradual progression in the prescribed frequency (number of times to perform the exercises that week), intensity (rate of exertion to perform the exercise that week) and duration (minutes to perform these exercises).

The exercises will conform with the new guidelines issued by the American College of Sports Medicine for people with an ostomy appliance [44]. Gradual progression also reduces the risk of participants over-exerting themselves with exercising and causing injury.

#### Who provides, how and where

Participants will receive a weekly physical activity consultation from an exercise instructor in-person, telephone and by video conferencing. The instructor will have as a minimum a Register of Exercise Professionals Level 4 recognised qualification (the instructor in this study for instance, has a cancer rehabilitation Level 4 qualification, and has a stoma and therefore has direct personal experience). All exercises are completed at home.

#### When and how much

The intervention is of 12 weeks duration. Each participant will receive a weekly consultation. The duration of each weekly consultation is likely to vary; based on our previous study, the average range is likely to be 15–45 min (min 5; max 120; median 35).

### Stage 2: feasibility study

#### Setting

Participants will be recruited from two hospitals in a National Health Service Trust/Board: Raigmore Hospital in NHS Highland (Scotland) and St James Hospital in Leeds Teaching Hospitals NHS Trust (England).

#### Eligibility criteria

PSH can give a person a bulge around the stoma, but some bulges do not correspond to PSH, which is an abnormal protrusion of the contents of the abdominal cavity through the abdominal wall defect created during placement of a colostomy, ileostomy or ileal conduit stoma [45]. Hence, adults 16 years+ (in the UK, for the purposes of research, people 16 years old and over are adults [46]); ≥ 3 months post stoma formation surgery for bowel disease (e.g., inflammatory bowel disease, colorectal cancer) with a colostomy or ileostomy who perceive that they have a bulge or PSH or who have a clinical diagnosis of PSH will be eligible. People who are already doing core training (e.g., Pilates, yoga) will be excluded. People with previous PSH repair will be excluded.

#### Intervention and comparator group

Participants randomly allocated to the intervention group will receive the physical activity intervention as described above and signposted to information and guidance about physical activity that are provided by UK relevant charities including Ileostomy and Internal Pouch Association and Colostomy UK. If allocated to the control group, participants will be signposted to the same guidance about physical activity.

#### Main outcome of feasibility study

The main outcome of this feasibility study is a decision by an independent Study Steering Committee to proceed to a full trial using the following traffic light system to guide decision-making (Table 1).

**Table 1 Tab1:**
[figure not shown]
Criteria for progression from feasibility to efficacy trial

#### Intervention measures and data collection

The following measures and data collection methods will be used to assess intervention parameters:

**Intervention fidelity**

Intervention fidelity is defined as the extent to which the intervention is delivered as intended by the exercise instructor [34]. The exercise instructor will record for each participant the number of consultations, duration and medium (e.g., face-to-face; video call; telephone call). Based on our previous study of a physical activity intervention for people with stoma [47], we estimate that the mean number of consultations will be 10 and mean duration approximately 35 min (mean duration per participant over 12 weeks is 322 min). The instructor will also keep a record of the exercise prescription each week, and make summary notes throughout the 12-week programme.

**Intervention adherence**

All exercises are completed at home. Intervention adherence is defined as the completion rate of the prescribed exercises by participants [36]. Participants will write down in a physical activity diary the frequency, intensity and duration of doing the core training exercises that are prescribed by the exercise instructor in a diary that they will complete each week for the 12-week duration. They will also record other types of leisure time physical activities that they do such as running, walking and swimming. Each day of the week, participants will report each type of exercise, their rate of perceived exertion using the Borg RPE Scale [48]. If more than one exercise is done in a given day, a separate row is used to record each individual activity.

A continuous rating scale will be used to assess participants’ adherence to the prescribed exercises. At the end of each week, participants will answer the following question:

‘On a scale of 0 to 10, how successful were you at completing the prescribed exercises? When answering this question think about your success in relation to the prescribed frequency, intensity and duration. A score of 10 indicates 100% successful.’

A free text box will be included in the diary so that participants can report any challenges and barriers that they encountered while performing the prescribed exercises.

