## Data management

Data will be kept in accordance with the Data Protection Act. The study includes four paper report forms: (i) Researchers in each site will complete a ‘recruitment form’ that will include number of eligible patients, the consent rate and reasons for declining participation; (ii) the clinical exercise instructor will complete a ‘consultation form’ indicating number, duration and type of consultation; (iii) participants will complete a diary to record prescribed activities; (iv) the study also includes the results of the clinical examination PSH classification and body composition. A researcher will remove patient names from any of these paper forms and replace with a unique identifier. Data on these paper report forms will be manually entered by a researcher into customised password encrypted spreadsheets in Microsoft Excel. A researcher will export all data entered into Microsoft Excel and Bristol Online Survey to the Statistical Package for the Social Sciences v19.0 for the purposes of analysis. All electronic data will be retained on a university password-protected server, and all paper records will be retained in a secure storage facility on university premises for a minimum of 10 years.

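### Adherence is defined as a completion rate, but the only instrument named to assess it is a merged 0-10 self-rating that cannot recover that rate

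*Protocol article*

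**What the plan says.** The definition, under Intervention adherence, is: "Intervention adherence is defined as the completion rate of the prescribed exercises by participants". Neither the unit (sessions, exercises or minutes) nor the denominator is given.

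The same section names the instrument: "A continuous rating scale will be used to assess participants’ adherence to the prescribed exercises". It is one question at the end of each week, "On a scale of 0 to 10, how successful were you at completing the prescribed exercises", with the instruction "When answering this question think about your success in relation to the prescribed frequency, intensity and duration" and one anchor, "A score of 10 indicates 100% successful".

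Two other records bear on the definition. Participants keep a diary for 12 weeks of how often, how hard and for how long they did the core exercises, with a free-text box for barriers. Under Intervention fidelity, "The instructor will also keep a record of the exercise prescription each week".

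Intervention measures and data collection introduces all of these methods together as means of assessing the intervention parameters. Data analysis says that adherence will be reported for the whole study and for each site, and that reasons for non-adherence will be summarised; it does not name the source. Data management lists four paper forms. The instructor's form is described as "indicating number, duration and type of consultation", and the diary as a record of prescribed activity.

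**The concern.** A completion rate is exercise done divided by exercise prescribed. The weekly item records neither term. It asks for a judgement of success across three dimensions and gives no rule for combining them, so participants who complete the same share of their prescription can answer differently, and participants who complete different shares can give the same answer.

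Adherence is one of the four intervention parameters in Aims, and it feeds the decision on a full trial. The Feasibility studies section itself says that adherence can affect the power and interpretation of a full trial, and that its definitions and cut-offs vary. A feasibility study that leaves two candidate quantities under one name gives its steering committee a figure whose meaning is unclear. Summarising reasons for non-adherence also needs a settled criterion for what counts as non-adherence.

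**Working it through.** The plan states no adherence figure to reproduce. The check sets the stated elements side by side and then asks whether the rating can yield the defined quantity.

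**Step 1: the elements**

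| Element | Source | Content |
|---|---|---|
| Defined quantity | Intervention adherence | Completion rate |
| Named instrument | Intervention adherence | Weekly 0-10 self-rating, three dimensions merged |
| Exercise done | Intervention adherence (diary) | Frequency, intensity, duration |
| Exercise prescribed | Intervention fidelity | Instructor's weekly record |
| Rule linking done to prescribed | None in the article | Not stated |
| Quantity to be reported | Data analysis | Adherence, source not named |

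Under What—procedures the prescription is individual and rises over the 12 weeks. The denominator therefore differs by participant and by week, and cannot be rebuilt without the weekly record.

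**Step 2: one week, several honest ratings.** Assumed inputs, not from the protocol: 5 sessions of 20 minutes prescribed; 3 sessions of 12 minutes done, at the prescribed exertion.

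- Session completion: 3/5 = 60%.
- Minutes per session: 12/20 = 60%. Exertion: 100%.
- Total minutes: (3 × 12)/(5 × 20) = 36/100 = 36%.
- Average of the three dimensions: (60 + 60 + 100)/3 = 73%.

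A participant who thinks in total minutes would answer about 3.6, one who thinks of the weakest dimension 6.0, and one who averages 7.3.

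**Step 3: one rating, different completion.** Assumed shares achieved of frequency, intensity and duration:

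| Shares | Session completion | Average × 10 | Weakest × 10 | Product × 10 |
|---|---|---|---|---|
| 100%, 100%, 50% | 100% | 8.3 | 5.0 | 5.0 |
| 50%, 100%, 100% | 50% | 8.3 | 5.0 | 5.0 |

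The two weeks get the same score under each of the three rules, yet session completion differs by a factor of two.

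**Step 4: range compatible with one score.** Suppose every participant averaged the three shares, each between 0 and 1. A score of 7 means that the shares sum to 3 × 0.7 = 2.1. The other two sum to at most 2, so the session share is at least 2.1 − 2 = 0.1, and it can be as high as 1. A score of 7 then fits session completion from 10% to 100%.

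The figures in steps 2 to 4 depend on the assumed inputs. That a single merged score cannot identify the rate does not.

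**The case against.** The strongest reply is that the diary comes directly after the definition, under the same heading, and that the opening sentence of the measures section counts it among the assessment methods. On that reading both diary and rating serve adherence, and the missing derivation belongs to a full protocol or analysis plan that is not shown. The item is also close to the definition: it asks about completing the exercises and is anchored at 100%. The article acknowledges that no standard adherence measure exists, and the diary is itself self-report.

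Much of this stands, and it rules out four stronger readings that a reader might infer:

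- *That the wrong parameter will be reported.* Data analysis does not say which quantity is reported.
- *That the prescription never reaches the dataset.* Data management summarises each form in a clause and does not say that the instructor's form holds nothing else. Its description of the diary could mean that the diary carries the prescription. All that can be said is that the prescription record is not explicitly listed.
- *That the item measures satisfaction.* It is a subjective estimate of completion.
- *That the failing dimension will be invisible, or that the committee will be misled.* The diary keeps the dimensions apart and has space for barriers. The content of Table 1 is not available in the text reviewed, so nothing can be said about how an adherence criterion is scaled.

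The illustration also shows that a completion rate has more than one form: 60% by sessions and 36% by minutes for the same week. The unit therefore has to be named.

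What the reply does not remove is the mismatch in the stated text. The section defines one quantity and names, as its assessment, an instrument for another. That is more than a derivation left to a later document.

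**Conclusion.** The point holds as a mismatch between definition and named measure. The article defines adherence as a completion rate, names a merged self-rating to assess it, collects records that would give the rate, and does not say that they will be combined or which quantity is the parameter.

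The size cannot be drawn from the plan. Under the assumed inputs, one week can honestly be rated from about 3.6 to 7.3, and a rating of 7 read as an average is compatible with session completion from 10% to 100%. No sample size, power or safety figure depends on this. The correction should be made because adherence informs the progression decision and the change is cheap. A full protocol or analysis plan that already names the diary-based rate would reduce this to a wording change in the article.

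**What to change.** Name the ratio of diary-recorded to prescribed core training sessions, per participant and week, as the adherence parameter. Show two components separately: minutes done over minutes prescribed, and exertion recorded against exertion prescribed. Make sure that the instructor's weekly prescription is entered and exported with the diary, for example as added fields on the consultation form. Keep the 0-10 item as a supportive measure of perceived success and describe its agreement with the diary-based rate.

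The cost is small. With about 10 of the 20 participants in the intervention group (equal allocation assumed), it comes to 10 × 12 = 120 participant-weeks of prescription data, with no new burden on participants. The diary remains self-reported and may have missing entries, so the number of participant-weeks with usable diary data should be reported beside the rate.
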